## Discussion

This protocol was designed to evaluate the impact of smoking and the use of other nicotine products on ED visits, including the respective clinical diagnoses and outcomes. Smoking is a leading preventable cause of morbidity and mortality. It is estimated that tobacco use accounts for 3%-6% of all ED visits and 5%-16% of total hospital expenses [28-30]. Smokers with preexisting diseases such as diabetes and asthma are more prone to ED visits than nonsmokers with similar conditions [23,31].

The smoking prevalence among patients at the ED surpasses that of the general population [16,18], indicating the ED as a key setting for managing smoking-related health issues. In recent years, there has been an intense debate about the harm reduction potential of ENDS. Some studies have shown their effectiveness in smoking cessation [32], yet there is scarce epidemiological evidence on the clinical impacts of noncombustible nicotine products. This study will be the first to explore the link between the use of various nicotine products and ED visits, as well as their association with urgent care needs for smoking-related disease.

Approximately one decade ago, our research group conducted the ECLAT study, which was the first randomized controlled trial that established the efficacy and the safety of e-cigarettes as smoking substitutes [33]. Since then, a newer generation of e-cigarettes, which are more efficient in nicotine delivery and more appealing, have shown encouraging results in clinical and real-world settings [34-41]. Therefore, they may represent a viable alternative for individuals unable or unwilling to quit smoking using approved methods. Nonetheless, it is important to thoroughly investigate and document the potential risk-reduction potential of these products in a clinical context.

Little epidemiological evidence exists on the harm reduction potential of ENDS. This study thus represents an opportunity to document epidemiological data on the link between the use of different nicotine products and disease severity during an ED visit, as well as clinical outcomes and associations with specific (ie, smoking-related) diseases. Besides further exploring the epidemiological impact of ENDS on diseases related to smoking, the implications of this study are also directly related to understanding the currently unknown burden of these products on emergency care resource use, particularly in the context of the well-known substantial effects of smoking on increasing ED visits. The systematic tracking of the impacts of nicotine use in this study will help to highlight the magnitude of tobacco and nicotine use in the community in relation to access to emergency health care services, and will enable those responsible for tobacco control policies, programs, research, and surveillance to assess the situation and inform decision-making.

This study, currently conducted in a single hospital, serves as a pilot phase, aiming to evaluate its feasibility and analyze the results. The ultimate objective is to expand this research to additional EDs within a national network.

Documenting the association between ENDS use and ED visits will provide insights on both local and central policy levels, especially when we consider that emergency and urgent care systems struggle with major challenges in developed countries with crowding, long waiting times, and, in general, increasing numbers of ED visits [42]. Therefore, it is important to examine factors associated with ED visits and adverse outcomes, and to assess if ENDS affect the ED burden in a different manner to smoking. At the same time, this study may document the need for routinely recording nicotine use habits for all patients accessing the ED instead of the current norm of recording smoking status only.

This study has several limitations. The brief period of recruitment and the use of only one study site may introduce sampling bias due to seasonality and locality. Therefore, this study may have limited generalizability to all Italian EDs. However, as mentioned above, this represents a pilot study with the purpose of further expanding the protocol to more regions and several EDs from other hospitals. While it is possible to verify exposure to tobacco smoke by measuring exhaled carbon monoxide and exposure to nicotine by measuring salivary cotinine, logistical and financial restrictions within the short duration of an ED presentation, as well as the urgent nature of attendance requested in the ED, preclude us from performing an objective assessment of the smoking status. Although self-report of smoking status has been shown to be accurate in the ED setting [17], a systematic review (despite including studies outside the ED setting) showed some discrepancy between self-report and objective assessment [43]. In addition, determining nicotine exposure would not help to distinguish between the use of tobacco cigarettes and noncombustible nicotine products. Moreover, the responses to questions on past smoking and nicotine use habits may be introducing recall bias. Finally, the exclusion of patients in a critical state who need urgent care will be compensated by a subsequent request to participate in the study once they are stabilized.

In conclusion, this study protocol addresses the need for additional epidemiological evidence on the effects of ENDS on health, with clinical endpoints. The ED setting represents an opportunity to record smoking and nicotine habits, assess the burden of different products, and provide guidance for interventions at both the personal and systematic level.

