**Conclusions:**

There is substantial debate about the harm reduction potential of alternative nicotine products in terms of their smoking-cessation and risk-reduction potential. This study represents an opportunity to document epidemiological data on the link between the use of different types of nicotine products and disease diagnosis and severity during an ED visit, and thus evaluate the harm reduction potential claims for these products.

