### Study Population

Inclusion and exclusion criteria are summarized in Textbox 1. Participants will be recruited among patients presenting at the ED of Policlinico Teaching Hospital of Catania, Italy, in 1 month during the diurnal shift. Only patients that access the ED for a nontraumatic reason will be screened, since it is unlikely that smoking or use of other nicotine products can have any causal effect on accident incidence and subsequent diagnosis. The study will take place during daytime working hours owing to organizational constraints. Typically, our ED admits approximately 70-80 patients for nontraumatic issues during a daytime shift, which runs from 8 AM to 8 PM.

We calculated the expected sample size for the study based on available national and regional statistics, providing a practical approach to estimating the study’s sample size. The current and former smoking rates in Sicily are estimated at 22.5% and 13.3%, respectively [25], while the combined prevalence of combustion-free products use (e-cigarettes and HTPs) stands at approximately 5% [26]. Considering the annual Catania ED access rate of 80,000 (monthly access rates of 6000-6500) [27], we anticipate recruiting no less than 1500 current smokers and 1000 former smokers per month. Additionally, we expect to enroll no less than 350 users of combined e-cigarettes/HTPs per month (dual usage is estimated at approximately 50% of the total). Since approximately 70 patients per day access the ED during the diurnal shift for nontraumatic reasons, we expect to enroll approximately 2000 participants in 1 month.

Inclusion and exclusion criteria for study participation.Inclusion criteriaAdult (aged≥18 years)Ability to understand and sign the informed consent formExclusion criteriaAccessed the emergency department for a traumatic accidentPregnancy

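### Conclusions on ED visits, ED burden and harm reduction go beyond a sample made up only of ED attenders

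*Protocol article*

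**What the plan says.** The operative sections of the protocol article are narrow. The Objective (Abstract) and the aim at the end of the Introduction concern severity and outcomes in patients visiting the ED. Endpoint and Outcomes makes the association of NEWS with use phenotype the primary endpoint. The secondary outcomes are admission, length of stay and a between-group comparison of six smoking-related acute diseases. Statistical Analysis plans chi-square tests, a Kruskal-Wallis test and regressions, all within the enrolled sample.

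The sampling frame, under Study Population, is equally clear: "Participants will be recruited among patients presenting at the ED of Policlinico Teaching Hospital of Catania, Italy, in 1 month during the diurnal shift". Trauma visits are excluded and written consent is required. Data Collection keeps only each person's first visit.

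The interpretive sections go wider. The Discussion opens with "This protocol was designed to evaluate the impact of smoking and the use of other nicotine products on ED visits" and says the study will be the first to "explore the link between the use of various nicotine products and ED visits". It later states "Documenting the association between ENDS use and ED visits will provide insights on both local and central policy levels", intends "to assess if ENDS affect the ED burden in a different manner to smoking" and addresses the findings to policy makers. The Conclusions of the Abstract say the study will "evaluate the harm reduction potential claims for these products".

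**The concern.** An association between product use and visiting the ED compares how often users and non-users attend. That needs people who did not attend, or a denominator of persons or person-time for each phenotype. In this study everyone attended, and repeat visits are dropped, so visit frequency among attenders is lost as well.

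What can be analysed is severity given attendance. Attendance depends on illness and, according to the Discussion, on smoking: it says that smokers with diabetes or asthma are more prone to ED visits than nonsmokers with similar conditions, and it calls the effect of smoking on ED visits well known. A NEWS contrast between ENDS users and smokers may therefore reflect who comes to the ED as well as how ill the two groups are.

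At stake is what the study may conclude. A lower NEWS in ENDS users could be reported to policy makers as lower ED burden or as support for harm reduction, which the data would not show. The planned expansion to 10-12 EDs would add attenders but no denominators. The limitations in the Discussion cover season, site, self-report, recall and critically ill patients, but not conditioning on attendance.

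**Working it through.** The article states no figure for visit risk, so there is none to reproduce. The check sets the claims against the data and then uses an arithmetic illustration.

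**Step 1. Claims against data.**

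| Claim in the article | What it needs | What is planned |
|---|---|---|
| Impact of products on ED visits (Discussion) | Attendance risk by phenotype | Attenders only, first visit only |
| ENDS and ED burden compared with smoking (Discussion) | Attendance times resource use per attender | Admission and length of stay per attender |
| Evaluation of harm-reduction claims (Abstract, Conclusions) | Risk of disease or severe events by phenotype | NEWS and diagnosis mix among attenders |

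The regional prevalences in Study Population (22.5% current smokers, 13.3% former smokers, about 5% users of combustion-free products) serve only the recruitment forecast. Statistical Analysis plans no comparison with them.

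**Step 2. Does the direction of the NEWS contrast fix the direction of visit risk?** All values here are assumed. A severe first attendance has NEWS 7 and a mild one NEWS 1. Counts are first attenders per 1000 persons, in line with the once-per-person rule.

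Mean NEWS = (7 × severe + 1 × mild) / (severe + mild). Attendance ratio = total / 50. Severe ratio = severe / 10.

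| Group | Severe | Mild | Total | Mean NEWS | Attendance ratio | Severe ratio |
|---|---|---|---|---|---|---|
| Smokers (reference) | 10 | 40 | 50 | (70+40)/50 = 2.2 | 1.0 | 1.0 |
| ENDS, case A | 10 | 90 | 100 | (70+90)/100 = 1.6 | 2.0 | 1.0 |
| ENDS, case B | 12 | 108 | 120 | (84+108)/120 = 1.6 | 2.4 | 1.2 |
| ENDS, case C | 5 | 20 | 25 | (35+20)/25 = 2.2 | 0.5 | 0.5 |
| ENDS, case D | 5 | 10 | 15 | (35+10)/15 = 3.0 | 0.3 | 0.5 |

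In cases A and B NEWS is lower while attendance is higher, and in B severe attendance is higher too. In case C NEWS is the same at half the attendance and half the severe cases. In case D NEWS is higher while attendance and severe cases are both lower. With only two NEWS values, a rank test moves with the severe share (20% in smokers; 10%, 10%, 20% and 33% in A to D), so using Kruskal-Wallis instead of means does not alter the point.

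**Step 3. What a visit-rate statement would need.** With ENDS share s among attenders and population prevalence p, the attendance ratio of users to non-users is [s/(1−s)] / [p/(1−p)]. Assume s = 5%:

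- p = 3%: (0.05/0.95)/(0.03/0.97) = 1.70
- p = 5%: 1.00
- p = 7%: (0.05/0.95)/(0.07/0.93) = 0.70

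The answer depends on an outside prevalence, which the article gives only as a crude approximate figure. Consent adds further selection: about 300 of 901 + 300 = 1201 approached did not consent, which is 25%.

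**The case against.** The strongest reply is that the plan itself already has the right estimand. No endpoint, hypothesis or test concerns a visit rate. The harm-reduction sentence in the Abstract follows a clause on diagnosis and severity during a visit, and burden can be read as resource use per attender, which admission and length of stay do measure. The study is called a single-centre pilot with limited generalizability. If NEWS is lower among ENDS users who attend, the hypothesis as written is supported, and the stated next step is multicentre replication, not a claim of lower burden.

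Most of this stands, and it confines the point to the interpretive text. It does not rescue the sentences on impact on ED visits, or on whether ENDS affect ED burden differently from smoking. These go beyond the planned analyses, and pilot status does not change that.

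Three stronger readings are tempting and are not supported:

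- **That the NEWS result will be biased in a known direction.** The illustration uses assumed counts, and the Introduction says ENDS use has not been systematically recorded in relation to ED visits. The effect of ENDS on attendance is unknown.
- **That visit risk could never be approached.** A crude comparison with regional prevalence is conceivable, but it is not planned. An age- and sex-standardized one cannot be made from the three crude figures given.
- **That the article presents prevalence of the six diseases as disease risk.** The term can be read as a proportion within the enrolled groups; it is only ambiguous.

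**Conclusion.** The point holds for the conclusions, not for the primary analysis, which can run as planned. The association of product use with ED visits, the comparison of overall ED burden and the evaluation of harm-reduction claims cannot be supported by within-sample comparisons of first-visit attenders. In the illustration, NEWS differences of −0.6, 0 and +0.8 against the smokers' 2.2 go with attendance ratios of 2.0 or 2.4, 0.5 and 0.3, so neither the sign nor the absence of a NEWS difference settles visit risk or harm.

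That visit risk is not estimable follows from the stated sampling and analysis alone. The illustration rests on assumed counts and NEWS values and shows only what is possible. The concern that attendance differs by phenotype rests on the article's own statements about smoking.

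**What to change.** 1. In the Conclusions of the Abstract and in the Discussion, confine the conclusions to severity, disposition, length of stay and diagnosis mix among enrolled ED attenders (consenting, daytime, nontraumatic, first visit), by use phenotype. This matches the Objective and the primary endpoint.
2. State that a difference, or no difference, in NEWS is not a difference in visit risk, overall ED burden or harm reduction.
3. In Endpoint and Outcomes, describe the six diseases as shares of enrolled ED presentations.
4. Add to the limitations that all comparisons are conditional on attendance, which smoking is said to increase and on which the effect of ENDS is unknown.
5. Do not add an age- and sex-standardized comparison with the cited regional prevalences, since only crude figures are given.

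The cost is rewording. Data, sample, endpoints and tests stay as they are, and the article reports that analysis is still pending, so the results report can carry the same limits. The downside is that the policy and harm-reduction claims narrow.

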## Appendix

Multimedia Appendix 1 Questionnaire to be administered to patients.

## Abbreviations

AVPU: alert, verbal, pain, unresponsive
eCRF: electronic case report form
ED: emergency department
ENDS: electronic nicotine delivery system
HTP: heated tobacco product
NEWS: National Early Warning Score
SMOPHED: Smoking or Nicotine Phenotype and Severity of Clinical Presentation at the Emergency Department
